### Study Outcome Measures

All outcome measures will be assessed online with validated German versions of the original questionnaires.

#### Primary Outcome Measure

Symptoms of depression will be assessed with the self-reported measure Patient Health Questionnaire–9 [37]. The Patient Health Questionnaire–9 has good diagnostic validity, sensitivity, and specificity and is a commonly used measure to assess and monitor depression severity [43].

#### Secondary Outcome Measures

Adherence is defined as the extent to which participants use the intervention. Following the suggestion of Donkin et al [44], a composite score encompassing time spent in the intervention, number of modules completed, number of exercises completed, number of log-ins, and number of clicks in the intervention will be used to measure adherence to the intervention. The composite score will be created by averaging the *z* scores of these indicators. Furthermore, and for exploratory purposes, we will also run the analyses with each of these indicators of adherence. Symptoms of anxiety will be assessed with the Generalized Anxiety Disorder–7 [45]. Symptoms of stress will be assessed with the stress subscale of the Patient Health Questionnaire [45]. Health-related quality of life will be assessed with the Short Form Health Survey–12 [46,47]. Suicidal ideation will be assessed with the Suicide Behaviors Questionnaire–Revised [38,39]. Problem solving will be assessed with the Social Problem Solving Inventory-Revised [48,49].

### Treatment Characteristics

Possible adverse effects of the intervention will be assessed with the Inventory for the Assessment of Negative Effects of Psychotherapy [50]. Client satisfaction will be measured with the Client Satisfaction Questionnaire [51,52]. System usability will be assessed with the System Usability Scale [53,54].

### Moderators and Mediators

Demographic information about participants will be assessed at baseline. Treatment expectancy will be assessed with the Credibility/Expectancy Questionnaire [55]. Working alliance with the online coaches will be assessed with the Working Alliance Inventory for Guided Internet Interventions [56].

### Randomization

The online platform Qualtrics (Qualtrics XM) randomizes participants in 2 steps. First, after T0 and before any contact with the study team, participants are randomized automatically to 1 of 4 groups (1, diagnostic interview and motivational interviewing module; 2, diagnostic interview; 3, motivational interviewing module; 4, no factor). The first randomization is stratified (either mild or moderate depressive symptoms). Second, after 2 weeks and completing T1, participants are randomized to 1 of 4 groups (1, guidance and email reminders; 2, guidance; 3, email reminders; 4, no factor). Both times, block randomization ensures a balance in sample size across groups over time. A schedule of enrollment and participation is shown in Table 2.

### Data Collection, Management, and Analysis

Participants complete questionnaires at all 5 time points online via Qualtrics. We manually invite participants to complete the baseline questionnaire (T0). The 4 subsequent time points (after 2, 4, 10, and 16 weeks) are automatically triggered once T0 is completed. We try to limit the amount of missing data from survey attrition by reminding participants after 5 and 10 days to complete the questionnaires.

### Statistical Analysis

Statistical reporting will follow CONSORT [57] and CONSORT-EHEALTH standards [58]. We will conduct primary analyses using intention-to-treat. The primary outcome is the change in Patient Health Questionnaire–9 score from baseline to 10 weeks and 16 weeks. Dropout rates are examined per condition. Before the analysis, we will examine baseline predictors of attrition. If it appears that attrition is related to measured aspects of the participants, we will include those measures as covariates in the models.

To test for the main and interaction effects of treatment components on primary and secondary outcomes, linear mixed model analysis of variance will be used. This approach uses all available data on each subject and does not involve the substitution of missing values but estimates parameters about missing values. However, sensitivity analyses will explore the impact of the imputation of missing values before computing the mixed models. The main effects and interactions will be based on aggregates across experimental conditions. The purpose of the factorial experiment is not to compare the 16 conditions to each other but to estimate the main effects of the 4 factors and interactions between the factors. For example, the main effect of the diagnostic interview will be estimated by comparing the mean of the experimental conditions in which this factor is present (conditions 1-8 in Table 1) versus the mean of the experimental conditions in which this factor is not present (conditions 9-16 in Table 1). No adjustment for multiple testing will be applied in the estimation of statistical significance because, in the optimization phase of the multiphase optimization strategy framework, the emphasis is on deciding what components will make up the optimized intervention [33]. Only a future RCT can then establish the superiority of the optimized intervention over other conditions.

### Power Analysis

We conducted an a priori power analysis for small-to-medium effect sizes (Cohen *d*=.35) for main effects and interactions between 2 factors (eg, guidance and diagnostic interview) on change in depressive symptoms (G-Power 3.1). From a clinical perspective, smaller effects are considered to be less relevant [59]. For type I error α=.05, with a common power of .80 to detect effects. Based on previous studies, we assume that our measurements regarding pre, post, and follow-up correlate at approximately *r*=.60. For a factorial design, this signifies a sample of n=204 to detect effects. Because we expect a dropout rate of about 20%, the planned sample size is n=255. For every condition, roughly 15 participants are required.

## Results

The study was registered at ClinicalTrials.gov (NCT04318236). The ethics committee of the canton of Bern (*Kantonale Ethikkommission Bern*) approved the study on January 20, 2020 (2019-01795). Recruitment started in February 2020. As of November 1, 2020, out of 1480 interested individuals, 409 individuals have completed T0, and 240 participants have been enrolled in the study.

## Discussion

### Overview

The primary outcome is depressive symptoms 10 weeks after baseline. Several secondary outcomes will be measured, such as symptoms of anxiety and stress, health-related quality of life, suicidal ideation, and problem solving. Possible moderating (age, gender, and adherence) and mediating (treatment expectancy, therapeutic alliance) effects will be tested. Furthermore, negative effects of psychotherapy, treatment satisfaction, system usability, and dropout rates will also be measured and inspected. This study builds on a wealth of encouraging efficacy studies of internet-based self-help. It promises to provide a more detailed insight into which supportive context factors enhance outcomes of and adherence to internet-based self-help interventions for depressive symptoms. Furthermore, the study may also inform about possible mediation and moderation effects that could provide more information about how or why internet-based self-help interventions for depressive symptoms work.

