**Objective:**

This study aims to better understand the effects of 4 supportive contextual factors on outcomes of and adherence to a web-based self-help program for depressive symptoms. In a factorial experiment, 2 of 4 supportive factors, for which there is evidence for their role on outcomes and adherence, are realized during the intervention—personal guidance and automated email reminders. The other 2 factors are realized before the intervention—a diagnostic interview and a preintervention module aimed at increasing the motivation to use the program with motivational interviewing techniques.

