**Methods:**

The study is a full factorial randomized trial. Adults with mild to moderate depressive symptoms (Patient Health Questionnaire–9 score: 5-14) are recruited from the community through the internet and conventional media. All participants receive access to a web-based self-help program based on problem-solving therapy. They are randomized across 4 experimental factors, each reflecting the presence versus absence of a supportive factor (guidance, automated reminders, diagnostic interview, preintervention module) resulting in a 16-condition balanced factorial design. The primary outcome is depressive symptoms at 10 weeks post assessment. Secondary outcomes include adherence to the program, anxiety, stress, health-related quality of life, possible negative effects, and treatment satisfaction. Potential moderators and mediators (eg, treatment expectancy, problem-solving skills, working alliance with the study team) will also be investigated.

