### Study Procedure

Interested participants can leave an email address on our study website [40]. Participants will automatically receive study information and an informed consent sheet (by email). After providing informed consent, participants are invited to complete the baseline assessment. Study eligibility is assessed and if included in the study, participants must wait 2 weeks before they can start with the intervention. Depending on which condition participants are randomized to, during these 2 weeks, participants either wait, are diagnostically interviewed, receive access to the preintervention motivational interviewing module, or receive both the interview and the preintervention motivational interviewing module (see Table 2).

**Table 2 table2:** Study flow and overview of study variables.

Study activity			Study period and timepoint											
			Allocation				Postallocation							Follow-up
			Week 0, T0		Week 0-2		Week 2, T1		Week 4, T2		Week 10, T3		Week 16, T4	

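### Adherence is listed as a moderator of the factor effects, although it accrues after both randomisations and is itself an outcome of the factors under study

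*Protocol article*

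**What the plan says.** The Overview in the Discussion of the protocol article states: "Possible moderating (age, gender, and adherence) and mediating (treatment expectancy, therapeutic alliance) effects will be tested". Other parts of the article fix what adherence is and when it arises.

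- **Definition.** Under Secondary Outcome Measures: "Adherence is defined as the extent to which participants use the intervention". It is scored as the average of z scores for time, modules, exercises, log-ins and clicks.
- **Status.** The Methods part of the Abstract says: "Secondary outcomes include adherence to the program, anxiety, stress, health-related quality of life". The Objective reads: "This study aims to better understand the effects of 4 supportive contextual factors on outcomes of and adherence to a web-based self-help program".
- **Timing.** Under Randomization, for the interview and the motivational module: "First, after T0 and before any contact with the study team, participants are randomized automatically to 1 of 4 groups". For guidance and reminders: "Second, after 2 weeks and completing T1, participants are randomized to 1 of 4 groups". Under Study Procedure: "participants must wait 2 weeks before they can start with the intervention".
- **Moderators elsewhere.** The Moderators and Mediators section of the Methods covers demographics, expectancy and working alliance, and does not name adherence. The Abstract gives expectancy, problem-solving skills and alliance as examples, again without adherence.

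**The concern.** A moderator analysis asks whether a factor's effect differs between kinds of participant. It keeps the protection of randomisation only if the moderator was settled before the factor was assigned. Age and gender meet that condition and adherence does not. A participant who reached a given level of use with reminders may have needed them to get there, while one who reached it without reminders did not. At equal adherence the two may differ in motivation and prognosis.

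Two results could mislead. The factor term in such a model is no longer the randomised effect. The interaction could also suggest that support works differently for high and low users when it does not. The Overview expects moderation and mediation results to shed light on how or why the interventions work, so readers may well draw on them.

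**Working it through.** **Timing and status.** The first randomisation follows T0. The second follows T1 at week 2. Program use opens after the 2-week wait. Adherence therefore accrues after assignment of all four factors. It is also a declared outcome, and the factors' effect on it is an objective.

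**Inputs.** The plan gives no figure for this analysis, nor any size for the factor–adherence, adherence–outcome or motivation links. Everything below except N is an assumption. N=204 is the sample before dropout in the Power Analysis section (204/0.80 = 255, as planned). Half, 102, are at each level of a factor.

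**Model.** F is the factor (0/1), U an unmeasured cause such as motivation (variance 1), A adherence and Y the outcome (lower is better). Residual SDs are 1.

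- A = a·F + k·U + e, where k may differ by factor level (k₀ absent, k₁ present)
- Y = c·A + u·U + e′, with no direct effect of F on Y

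The analysis regresses Y on F, A (standardised) and F×A.

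**Additive shift (k₀ = k₁ = k).** Given A and F, the expected U is k(A − aF)/(k² + 1). The factor term therefore carries a bias of −u·k·a/(k² + 1), and the slope on A is the same at both levels, so no interaction arises.

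- a=0.5, k=0.5, u=−0.5: 0.5×0.5×0.5/1.25 = **+0.10**
- a=0.5, k=0.7, u=−0.7: 0.7×0.7×0.5/1.49 = **+0.16**

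**Changed link (k₀ ≠ k₁).** With c=0 the slope of Y on A is u·k/(k² + 1) at each level. The interaction is the difference in slopes times the pooled SD of A.

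- k 1.0 to 0.3, u=−0.7: slopes −0.350 and −0.193, difference 0.157. SD of A = √[(2 + 1.09)/2 + 0.0625] = 1.268. Interaction 0.157×1.268 = **+0.20**
- k 0.8 to 0.2, u=−0.7: slopes −0.341 and −0.135, difference 0.207. SD of A = √[(1.64 + 1.04)/2 + 0.0625] = 1.184. Interaction 0.207×1.184 = **+0.25**

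**Simulation.** 4,000 trials per row, N=204, two-sided 0.05. Percentages are rejection rates.

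| Assumed truth | Unconditional factor effect | Factor term given A | F×A |
|---|---|---|---|
| F affects neither A nor Y (k=0.5, u=−0.5) | 0.00 (5.1%) | 0.00 (4.8%) | 0.00 (5.3%) |
| F raises A by 0.5, no effect on Y (k=0.5, u=−0.5) | 0.00 (4.3%) | +0.098 (8.9%) | 0.00 (4.6%) |
| Same, stronger motivation (k=0.7, u=−0.7) | 0.00 (5.3%) | +0.165 (17.3%) | −0.01 (5.2%) |
| Same, link weakened, k 1.0 to 0.3 | 0.00 (4.9%) | +0.141 (14.0%) | +0.199 (20.9%) |
| Same, link weakened, k 0.8 to 0.2 | 0.00 (5.5%) | +0.113 (9.8%) | +0.246 (28.9%) |
| Effect wholly through A (c=−0.7), no U effect on Y | −0.346 (48.9%) | 0.00 (4.1%) | 0.00 (4.6%) |
| Same, with U effect on Y (k=0.5, u=−0.5) | −0.346 (38.2%) | +0.101 (10.0%) | 0.00 (4.4%) |

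The simulation matches the formulas. In the last two rows the true direct effect is zero. The 0.00 is therefore a correct direct effect, although it is not the factor's total effect of about −0.35 (0.5×−0.7). Only the +0.10 is bias.

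**The case against.** The strongest reply is that this is one clause in a Discussion, hedged as possible and with no model given. The Methods section on moderators does not name adherence, and a fuller plan may handle it properly. That limits the weight of the point but does not remove it, because the sentence says these effects will be tested and places adherence beside two baseline traits.

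Four stronger readings are tempting, and the documents do not support them.

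- *The interaction test is confounded whatever happens.* With a purely additive shift in adherence it stays near zero and near 5% rejection. A false interaction needs the factor to change the link between motivation and adherence. That is plausible for reminders, since prompts go to people who have not logged in for a week, but no value is given.
- *The reported factor effects are spoiled.* The Statistical Analysis section estimates main effects by comparing conditions with and without a factor, and does not adjust for adherence.
- *Every factor is predicted to raise adherence.* The Objective is to understand such effects. The Introduction reports direct comparisons of guidance with no significant difference in modules completed, and calls the evidence on reminders limited.
- *Adherence is shown to be a mediator.* It may be one, but that needs an effect of adherence on outcome, which the documents do not establish. Most rows of the table assume none.

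**Conclusion.** The point holds in a limited form. The Overview names as a moderator a variable that arises after both randomisations and that the study also treats as an outcome of the factors. The factor term conditional on adherence is biased as an effect if unmeasured causes drive both adherence and outcome and the factor moves adherence. A false interaction can arise if the factor also alters how those causes relate to adherence. The illustrative sizes are a bias of 0.10 to 0.16 residual SD under an additive shift and, where the link changes, a false interaction of 0.20 to 0.25 declared in 21% to 29% of trials. All rest on assumed links and on a product-term model that the article does not specify. The sample size and the primary factor comparisons are unaffected. This is a fault in a secondary analysis that should be corrected, not a threat to the main result.

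**What to change.** Remove adherence from the moderators in the Overview. Limit moderators to variables measured before the randomisation of the factor concerned. Age and gender qualify for all four factors. T1 measures precede assignment of guidance and reminders but follow assignment of the interview and the motivational module, so they could serve only for the former pair. No further moderators need to be added.

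Keep adherence as the secondary outcome it already is. If its part in the effect is of interest, analyse it as a mediator, adjusting for baseline confounders, with a sensitivity analysis for unmeasured confounding, and label the result exploratory.

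Align the Methods part of the Abstract, the Moderators and Mediators section and the Overview so that each variable has one stated role.

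The deletion and alignment are wording changes and need no new data. The mediation analysis, if done, adds some analysis work and still depends on assumptions about confounding.

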### Strengths and Limitations

Our study has been designed to shed more light on the supportive context of internet-based self-help interventions. It deconstructs a treatment package and explores active and inactive supportive factors. Understanding which factors do and do not work will help us get closer to the goal of delivering internet-based self-help interventions optimally. According to the guidelines of multiphase optimization strategy, a future RCT should test an intervention providing an optimal supportive context based on our findings, against an intervention providing a context that is usual in studies about internet-based self-help interventions (eg, an intervention with guidance). With such a study, the possible superiority of the optimized context could be established.

Limitations of this study are comparable to those of the majority of studies about internet-based self-help interventions. The sample of this study is self-selected and participants become aware of our study through the internet. This limits the generalizability of possible findings to regular clinical settings or individuals that rarely use the internet.

### Conclusion

To improve outcomes to future internet-based self-help interventions for depression, this study could provide recommendations on how to optimize the context of human and automated support. Based on findings of active and inactive factors and the interactions thereof, recommendations could be made for future research and the implementation and dissemination of internet-based self-help interventions in routine care.

## Abbreviations

CONSORT: Consolidated Standards of Reporting Trials
CONSORT-EHEALTH: Consolidated Standards of Reporting Trials of Electronic and Mobile Health Applications and Online Telehealth
HERMES: Herausforderungen meistern (overcoming challenges)
RCT: randomized controlled trial
